## 2. Study design and endpoints

### 2.1 Study design

DREAM is a phase 2 b efficacy monocenter, prospective, **randomized, controlled double blinded trial**, comparing intra-discal autologous adult BM-MSC therapy and sham treated controls in subjects with chronic LBP (> 6 months) due to lumbar multilevel IDD (max. 3 levels) unresponsive to conventional therapy. Patients will be randomized in 2 arms of 26 patients and followed up for 24 months.

[figure not shown]

Figure 4 - Study design

DREAM will use autologous BM-MSC expanded according to validated and approved IMPD, using same cell process as in a previous assay authorized by EMA and performed by members of the consortium.

Bone marrow will be obtained from the patients after inclusion in the study and informed consent signature. The sham group will undergo percutaneous puncturing, without the needle gets to the iliac crest and without bone marrow withdrawal.

## **2.2 Randomization**

The randomization will be centralized and stratified on the investigation center, and on the current attending to a rehabilitation program at the inclusion visit. It is performed 24 hour-a-day online by the central randomization web-service. To randomize a patient, investigators have to login, enter the patient identification, additional checks and factor values. Since patients are assigned to the centre, the randomizing investigator is currently in the system. The patient identification must be unique within all randomizations performed. If everything is entered correctly, a summary of the patient data including the randomization result is shown. For double-blind trial the randomization result will be a treatment code. The Investigator in charge of injections will not have any discussion about treatment allocation with patients and clinical observers. The PI won't have access to the list of treatment codes used for blinding. Thereby will transmit the treatment code of the patient to each local pharmacy.

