### **1.3 Justification of the route administration, dosage and treatment period**

Autologous BM-MSC will be administered via imaging control into the discs affected by IDD where they are expected to exert their therapeutic effects. As we mentioned above, no current standard treatments are available to influence the course of the disease and no drugs/devices brought significant proofs to limit the structural IDD. In the previous studies, a median dose of  $15 \times 10^6$  of MSC was injected with a good outcome and without side effects. Thus, we decided to use a dose of  $15 \times 10^6$  of autologous BM-MSC each disc in the active arm and a sham procedure in the control group without active product.

Several studies have reported that BM-MSC injection is safety, without adverse events [Orozco et al., 2013] [Vega et al., 2015]. Mild adverse reactions, such as pain, have been reported for both groups (sham and treated) without statistically significant differences.

The possibility to treat 3 different discs, each one with the selected dose ( $15 \times 10^6$ ), has been decided according to the results of a recent Phase I clinical study where  $50 \times 10^6$  Adipose derived stem cells were intrarticularly injected without adverse events [Pers et al., 2016].

Based on previous recommended papers, it seems the best option to check efficacy in chronic LBP is a period of more than 6 months. Thus, we retained as primary outcome an improvement of pain and functional status 12 months after treatment.

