## **2.3 Objectives**

### **2.3.1 Primary objective:**

- Evaluate the effectiveness of intradiscal injection of autologous BM-MSCs in reducing chronic LBP due to multilevel (max. 3 levels) lumbar IDD after 24 months of treatment in terms of pain relief (VAS), functionality (ODI) and quality of life (SF36).

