#### **3.1 Inclusion criteria**

- Age between 18 and 65 years.
- Signed informed consent.
- Symptomatic chronic LBP due to moderate IDD [modified Pfirrmann score 3-4 (Pfirrmann et al., 2001), Griffith score 3-7(Griffith et al., 2007)] at max.3 levels of the lumbar spine unresponsive to conservative treatment, physical and medical for at least 6 months. Physical treatment includes physiotherapy. Medical treatments includes NSAID, paracetamol, opioids and myorelaxant. (For more details, see paragraph 1.1.4).
- Annulus fibrosus intact, demonstrated by MRI.
- Pain baseline > 40 mm on VAS (0- 100).NSAID washout of at least 2 days before screening.
- NSAID washout of at least 2 days before screening.

- Painkillers washout of at least 24 hours before screening.
- For females of childbearing potential (see definitions in paragraph 6.5), a negative pregnancy test must be documented at Screening.
- Men and women should use effective contraception during treatment and for at least 24 months after BM-MSD discontinuation. The complete list of contraceptive methods is described in the patient information sheet and in the paragraph 6.5. As a precautionary measure, breast-feeding should be discontinued during treatment with BM-MSD and should not be restarted after discontinuation of BM-MSD.

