### 3.2 Exclusion criteria

- Congenital or acquired diseases leading to spine deformations that may upset cell application (scoliosis, isthmus lesion, sacralization and hemisacralization, degenerative spondylolisthesis).
- Spinal segmental instability assessed by dynamic X-Ray.
- Symptomatic facet joints syndrome on MRI (facet joints hyperintensity and hypertrophy evaluated at coronal T2 weighted MRI).
- Prior to the screening visit, has received:
  - Oral corticosteroid therapy within the previous 3 months, OR
  - Intramuscular, intravenous or epidural corticosteroid therapy within the previous 3 months
- Presence of a 4th level with symptomatic IDD (modified Pfirrmann score 3-4, Griffith score 3-7) in the lumbar spine.
- Spinal canal stenosis (Schizas score > B).
- History of spinal infection.
- Lumbar disc herniation and sciatica.
- Endplate abnormality such as Schmorl's Nodes.
- Previous discal puncture or previous spine surgery.
- IDD with Modic II and III changes on MRI images.
- Patients not eligible to the intravertebral disc surgery.
- Patients who have the risk to undergo a surgery in the next 6 months.
- Patients with local infusion device/devices for corticosteroids.
- Obesity with body mass index (BMI in Kg/size in m^2) greater than 35 (obesity grade II).

- Participation in another clinical trial or treatment with another investigational product within 30 days prior to inclusion in the study.
- Abnormal blood tests: hepatic (alanine aminotransferase [ALT] and/or aspartate aminotransferase [AST]  $>1.5 \times$  upper limit of normal [ULN]), renal, pancreatic or biliary disease, blood coagulation disorders, anemia or platelet count of  $<100 \times 10^9/L$ .
- Pregnant or lactating women, or premenopausal women not using an acceptable form of birth control, are ineligible for inclusion. Contraception will be maintained during treatment and until the end of relevant systemic exposure. Additional pregnancy testing will be performed at the end of relevant systemic exposure. The patients will be required to use contraception from initial treatment administration until 24 months after the last dose of study drug.

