### **6.2.5 Day 0 - Visit 0: Visit baseline and treatment**

- Physical exploration
- Vital signs (Temp, BP, HR)
- Lateral MRI, T2, quantitative
- Medication history therapy
- Blood sampling for routine laboratory testing
- Urine analysis

- Pain assessment of the lumbar spine by visual pain scale (VAS)
- Oswestry Disability Index in order to measure a patient's permanent functional disability, Quality of life assessment using SF-36
- Instruction for wash out (NSAIDS washout of at least 2 days before this screening Visit, no painkillers 24h before the visit)
- Prohibition of NSAIDs
- Adverse event assessment
- Concomitant medication
- Intervention : injection of autologous cells or sham procedure (under fluoroscopy guide and monitor cell implantation). The affected disks (max 3) are treated simultaneously once only, at the V0 visit and no subsequent doses are expected.

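### Randomisation stratifies on centre in a one-centre trial and leaves number of affected discs unbalanced, while eligibility admits single-level patients to a trial whose objective is multilevel disease

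*Protocol*

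**What the plan says.** On stratification, section 2.2 of the Protocol reads: "The randomization will be centralized and stratified on the investigation center, and on the current attending to a rehabilitation program at the inclusion visit". Section 2.1 opens with "DREAM is a phase 2 b efficacy monocenter, prospective", and the synopsis agrees that there is one centre.

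On the population, the primary objective in section 2.3.1 is "reducing chronic LBP due to multilevel (max. 3 levels) lumbar IDD after 24 months of treatment". Sections 1.2 and 2.1 also speak of multilevel disease. The inclusion criterion in section 3.1 asks for degeneration "at max.3 levels of the lumbar spine unresponsive to conservative treatment, physical and medical for at least 6 months". The only exclusion in section 3.2 that turns on the number of levels is "Presence of a 4th level with symptomatic IDD". No lower limit appears in either list.

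On exposure, section 1.3 refers to "The possibility to treat 3 different discs, each one with the selected dose", and section 6.2.5 says "The affected disks (max 3) are treated simultaneously once only, at the V0 visit".

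On timing, sections 6.1 (note d) and 6.2.1 put the MRI used for disc grading at pre-screening, before randomisation in section 6.2.3.

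On adjustment, section 7.2 foresees a multivariable regression, among the sensitivity analyses, for covariates that turn out not to be comparable at baseline. It does not name number of discs.

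**The concern.** Two statements in the Protocol do not fit the rest of it. A stratification factor with one level creates no strata, so the scheme has one working factor where it appears to have two. And a trial made up largely of single-level patients would satisfy every eligibility criterion without addressing the multilevel population that the objective names.

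The two problems meet in one variable. Number of affected discs describes extent of disease in every patient, whichever arm they join, and is plausibly related to a response scored once per patient. With 26 per arm it can easily split unevenly by chance. At stake are the precision and readability of the primary comparison and, more importantly, which population the result can be said to apply to.

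**Working it through.** **1. Working strata.** Centre (1 level) × rehabilitation attendance (2 levels) = 2 strata, averaging 52/2 = 26 patients. This is the same scheme as stratifying on rehabilitation alone.

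**2. Levels, side by side.** Objective, design and rationale (2.3.1, 2.1, 1.2): multilevel, at most 3. Eligibility (3.1, 3.2): at most 3, no minimum. The admissible counts are therefore 1, 2 and 3. The cap in 2.3.1 limits the count from above; it does not turn multilevel into one or more.

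**3. What disc count determines.** In both arms it gives the extent of disease. In the active arm only, it also sets total cells. Section 5.3 gives 7.5 × 10^6 cells/mL × 2 mL = 15 × 10^6 per syringe, and 3 × (15 ± 1) = 45 ± 3 × 10^6, which reproduces the stated total. One, two or three discs thus means 15, 30 or 45 × 10^6 cells. (Section 1.5 writes the per-disc figure as a concentration per mL, which does not agree with 5.3 and must be reconciled; I use 1.3, 5.3 and 5.5.)

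**4. Chance imbalance.** Inputs: 52 patients in two arms of 26 (2.1). The single-level share is not given, so I assume 20% to 50%. With K single-level patients among 52, the number X in one arm is hypergeometric (52, K, 26), and the arms differ by |2X − K|. The rehabilitation stratum is ignored.

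| Assumed share | K | P(differ by 4 or more) | P(differ by 6 or more) |
|---|---|---|---|
| 20% | 10 | 0.291 | 0.075 |
| 30% | 16 | 0.368 | 0.132 |
| 40% | 21 | 0.258 | 0.089 |
| 50% | 26 | 0.406 | 0.165 |

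The values do not rise steadily because the difference has the same parity as K: for K = 21, a difference of 4 or more means 5 or more, and 6 or more means 7 or more. Four patients is 4/26 = 15 percentage points of an arm; six is 6/26 = 23.

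**5. Effect on the estimate.** Shift = imbalance in share × difference in response between single- and multi-level patients, the latter taken as equal in both arms. The Protocol gives no such difference, so I assume 10 to 20 points:

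- 0.231 × 0.10 = 0.023, about 2 points
- 0.231 × 0.20 = 0.046, about 5 points

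**6. Scale.** At the planning rates in section 7 (30% and 68%), the standard error of the difference is √[(0.30 × 0.70 + 0.68 × 0.32)/26] = √(0.4276/26) = 0.128, or 12.8 points. A shift of 4.6 points is 4.6/12.8 = 0.36 standard errors, against a planned difference of 38 points.

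**7. After the change.** Disc count (1 versus 2–3) × rehabilitation (2 levels) = 4 strata, averaging 52/4 = 13 patients.

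**The case against.** The strongest reply is that a one-level factor does no harm, that stratifying on disc count is a preference, and that the multilevel wording is loose drafting. Randomisation is valid without disc count in the scheme. Age, baseline pain and grade are not stratified either, and 52 patients support few factors. Section 7.2 already plans a regression for covariates that look unequal. The shift in the estimate rests on two assumed inputs, can go in either direction, and is ordinary sampling variation already inside the standard error. Sections 1.3 and 1.5 present three discs as a ceiling, in line with 3.1.

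Much of this stands. It keeps the point from being critical. It does not remove the mismatch between objective and eligibility, nor the factor that balances nothing. Section 7.2 is only a partial safeguard, because it selects covariates after imbalance is seen and only as a sensitivity analysis.

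A reader might infer from the threefold range in total cells that unequal dose contaminates the comparison between arms. The documents do not support that. Sections 1.7 and 5.6 give sham patients no disc injection, so cells and disc punctures vary only within the active arm and cannot be unbalanced between arms. The fixed amount per disc is how the intervention is defined. Only disease extent can be unbalanced. Nor can one infer that single-level patients will dominate: no distribution is given, and the criteria merely allow it.

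**Conclusion.** The concern holds as two drafting errors with one cheap design improvement attached. Centre is a void stratification factor in a one-centre trial. The stated objective and the eligible population disagree on the minimum number of levels. Disc count, available before randomisation, is neither balanced nor named for adjustment.

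The trial is not biased and its test is not invalid. The cost is a chance of roughly one in four to two in five of a 15-point or larger imbalance in the single-level share, and about 7.5% to 16.5% of a 23-point or larger one, if that share lies between 20% and 50%. The larger imbalance would move the estimate by about 2 to 5 points under the assumed 10- to 20-point difference in response, well below one standard error. The mismatch of populations rests on no assumption, and matters more for what the trial can conclude.

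**What to change.** In section 2.2, delete centre and stratify on number of affected discs (1 versus 2–3), fixed from the existing MRI before randomisation, alongside rehabilitation attendance. If randomisation has begun, leave the scheme alone and prespecify disc count as a baseline covariate, whatever balance is observed.

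Reconcile sections 1.2, 2.1, 2.3.1 and the synopsis with sections 3.1 and 3.2, so that objective and eligible population state the same range of levels. Which passage gives way is for the sponsor. If single-level patients end up outside the population, the 1 versus 2–3 split no longer applies and the remaining counts would define the factor.

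Cost: one field changed in the web randomisation set-up, and wording in a few sections. The required sample size is unchanged. The downside is small: the disc count must be recorded before randomisation, and there are four strata averaging 13 patients, with smaller ones if single-level patients are few (at 20%, about 10 patients shared between two rehabilitation strata).

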## **2.3 Objectives**

### **2.3.1 Primary objective:**

- Evaluate the effectiveness of intradiscal injection of autologous BM-MSCs in reducing chronic LBP due to multilevel (max. 3 levels) lumbar IDD after 24 months of treatment in terms of pain relief (VAS), functionality (ODI) and quality of life (SF36).

### **2.3.2 Secondary objectives:**

- Evaluate regenerative changes of the treated IVD.
- Assess modification of employment and work status between baseline and months 12 and 24.
- Assess safety and tolerability.
- Evaluate consumption of medications to relieve pain such as type and dose of analgesics.

## **2.4 Endpoints**

### **2.4.1 Primary Endpoint:**

- To evaluate the efficacy of intradiscal injection of autologous BM-MSC using the visual analog scale (VAS) and functional status assessed by the Oswestry disability index (ODI) after 24 months of treatment, defining

responders in case of at least 40% improvement in VAS or ODI at month 24 compared to baseline.

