#### **2.4.2 Secondary Endpoint:**

- To evaluate changes of the treated IVD induced by regenerative therapy by quantitative Magnetic Resonance Imaging (MRI) signal measurements in T2, T1spin/echo, and T1rho weighted images that allow a quantitative measure of the NP extracellular matrix.
- To evaluate modification of disability (ODI) and quality of life (SF-36 scores) considered as continuous measures, between baseline and 1, 3, 6, 12 and 24 months.
- Safety and tolerability will be evaluated by recording adverse events (AEs) and serious AEs (SAEs) throughout the study till 24 months. Number of participants with adverse events, the correlation of the AE to the IMP and their severity will be used as a measure of safety and tolerability.
- To evaluate consumption of medications to relieve pain such as type and dose of analgesics will be evaluated. Paracetamol (acetaminophen) and levels 2 analgesics will be assessed throughout the study at each visit.

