## **4. Measurement of outcomes**

### **4.1 Primary Outcome Measures:**

The clinical response is defined as pain relief of at least 40% and 40 mm decrease on VAS scale between baseline and month 24, or 40% improvement of functional index ODI at month 24 compared to baseline. Chronic LBP is assessed using the VAS pain scale (0 – 100, where 0 represents no pain and 100 represents the worst pain imaginable). ODI scale ranges from 0 to 50 and allows evaluation of disability (0% – 20%: minimal disability; 20% – 40%: moderate disability; 40% – 60%: severe disability; 60% – 80%: crippled; 80% – 100%: bed-bound or exaggerating their symptoms).

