| Checking inclusion and exclusion criteria                           |                | X           |                             |                  |                       |                       |            |             |              |              |
| Randomization                                                       |                |             | X                           |                  |                       |                       |            |             |              |              |
| Pain lumbar spine (VAS), ODI, SF-36                                 | X              | X           |                             | X                | X                     | X                     | X          | X           | X            | X            |
| Lateral MRI, T2, quantitative                                       | X d |             |                             |                  | X                     |                       |            | X           | X            | X            |
| Adverse Events                                                      |                |             |                             |                  | X                     | X                     | X          | X           | X            | X            |
| Concomitant medication                                              |                | X           |                             | X                | X                     | X                     | X          | X           | X            | X            |

a: NSAIDs washout of at least 2 days before screening, inclusion and baseline. NSAIDs will not be authorized during the first 6-month after baseline. However, if needed after the first 6 months, NSAIDs could be used

b: Patients will be required to refrain from taking paracetamol or opioids within 24 hours of each clinical visit for efficacy evaluations

c: vital signs: Temperature, heart rate, arterial blood pressure, height, weight

d: MRI was also used to assess the Pfirrmann and Griffith's score

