## **7. Statistic analysis planning and power calculation**

Sample size was calculated to have 80% power and 2 balanced groups and according to the literature data (Maher et al., 2017; PopulationReferenceBureau; 2016), a responder rate is expected at 12 months of the order of 30% in controls and 68% for MSC is a delta of 38% between the two groups. To highlight this

difference while justifying a power of 80% and an alpha risk of 5% and within 1:1 ratio, taking into account 20% of inclusion failure, it is necessary to include 26 individuals per group a total of 52 subjects.

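### VAS pain, part of the primary objective, has no defined continuous endpoint: section 2.4.2 lists ODI and SF-36 only, and section 7.1 names tests of means for a yes/no primary endpoint

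*Protocol*

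**What the plan says.** Protocol section 2.3.1 frames the primary objective at 24 months "in terms of pain relief (VAS), functionality (ODI) and quality of life (SF36"). Section 2.4.1 turns two of those three measures into one yes/no outcome: "responders in case of at least 40% improvement in VAS or ODI at month 24 compared to baseline". Section 4.1 words the VAS part more strictly: "The clinical response is defined as pain relief of at least 40% and 40 mm decrease on VAS scale between baseline and month 24", with a 40% ODI improvement as the alternative.

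Among the secondary endpoints, section 2.4.2 reads "To evaluate modification of disability (ODI) and quality of life (SF-36 scores) considered as continuous measures", at 1, 3, 6, 12 and 24 months. VAS is not in that line. Section 4.2 has a paragraph on pain under the secondary outcome measures. It describes a 10 cm line, the reading in centimetres, and separate readings at rest and in motion. It stops at measurement.

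The visit table in section 6.1 has one row, "Pain lumbar spine (VAS), ODI, SF-36", marked at baseline and at every follow-up visit. Section 7 sizes the trial on responder rates: "a responder rate is expected at 12 months of the order of 30% in controls and 68% for MSC". Section 7.1 plans to evaluate the treatment effect by analysis of variance and Student's t test and names no comparison of proportions.

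**The concern.** The primary objective has three measures. ODI and SF-36 each get a continuous endpoint with stated time points. VAS, the pain measure itself, does not. As the text stands, the size of the pain effect in millimetres has no pre-specified endpoint. A reader of the final report could not tell whether a VAS analysis at a given month was planned or chosen later.

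The responder rule is a coarse substitute, and the protocol gives no reason for 40%. No ODI minimum is set for entry, so a fall from 5 to 3 on the 0-50 scale (2/5 = 40%) counts as response. A VAS fall from 80 to 50 mm (30/80 = 37.5%) with a 39% ODI improvement does not. Sections 2.4.1 and 4.1 also disagree on whether a 40 mm fall is required. A fall from 80 to 45 mm (35/80 = 44%, but 35 mm) meets the VAS criterion in 2.4.1 and not the one in 4.1. A continuous VAS endpoint would not depend on how that conflict is settled.

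Section 7.1 adds to the uncertainty. It names methods for means, but the protocol defines no continuous primary variable to which they could apply.

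**Working it through.** **1. Which measures have which endpoint**

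| Measure | In primary objective (2.3.1) | In responder rule (2.4.1) | Continuous endpoint (2.4.2) | Collected at each follow-up visit (6.1) |
|---|---|---|---|---|
| VAS | yes | yes | no | yes |
| ODI | yes | yes | yes | yes |
| SF-36 | yes | no | yes | yes |

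VAS is the only one of the three without a continuous endpoint, and the cause is the endpoint list, not the data collection.

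**2. The plan's own sample size.** Inputs from section 7: 30% and 68%, 80% power, 5% alpha (sidedness not stated), 1:1. With pooled variance, mean rate 0.49:

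n = [1.960 × √(2 × 0.49 × 0.51) + 0.842 × √(0.30 × 0.70 + 0.68 × 0.32)]² / 0.38² = (1.386 + 0.550)² / 0.1444 = 26 per arm.

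So 26 is the two-sided figure before any allowance for loss. If the stated 20% is lost, 26 × 0.8 ≈ 21 per arm remain. (A one-sided test gives 21, and 21 × 1.2 = 25.2, rounded up to 26. The sample-size text is a separate matter and sets only the two values of n used here.)

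**3. Responder power, two-sided.** Φ[(0.38√n − 1.386) / 0.654] gives Φ(0.844) = 80.1% at n = 26 and Φ(0.544) = 70.7% at n = 21.

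**4. Full-scale power under one assumed model.** Assume improvement is a single normal score with equal SD in both arms, cut at the same point. The shift is d = z(0.68) − z(0.30) = 0.468 + 0.524 = 0.992 SD. With noncentrality d√(n/2) = 3.58 and 3.21, the two-sample t test has power 93.9% at 26 per arm and 88.0% at 21. The differences from step 3 are 13.8 and 17.3 points. For 80% power the full scale needs about 16 per arm (normal approximation) or 17 (noncentral t), against 26, so in this model the cut keeps roughly 60 to 65% of the information.

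**5. Allowing for the either-scale rule.** If 30% and 68% are rates for VAS or ODI, the shift on one scale is smaller. Take two normal scores with correlation ρ, a common cut and a common shift, solved so that the union is 30% and 68%. Power for one scale (normal approximation) minus responder power, two-sided, in points:

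| ρ (assumed) | 0 | 0.3 | 0.5 | 0.7 | 0.9 |
|---|---|---|---|---|---|
| shift per scale, SD | 0.815 | 0.873 | 0.909 | 0.943 | 0.976 |
| 26 per arm | 3.6 | 8.2 | 10.5 | 12.5 | 14.0 |
| 21 per arm | 4.6 | 10.1 | 13.1 | 15.7 | 17.9 |

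One-sided, the gain is 2.0 to 8.8 points at 26 per arm and 2.9 to 12.4 at 21. Overall this is about 2 to 18 points.

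**6. Other shapes (simulation, two-sided).** With a t distribution on 3 degrees of freedom, a rank test has about 83% power at 26 per arm and 76% at 21, a gain of about 3 to 6 points. The unadjusted t test has about 69% and 61%, roughly 10 points below the responder test. Next, take a mixture in which each patient either improves a lot or hardly at all (assumed mean improvements of 60-70% and 5-10%, within-group SD 15-20, calibrated to 30% versus 68%). At 26 per arm the t test has about 76 to 82% against 78 to 79% for the chi-square test, and the rank test can fall below the responder test.

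**The case against.** The strongest case against has four parts.

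First, a reader might infer that VAS is absent from the plan on its own scale. It is not. Section 4.2 lists VAS pain among the secondary outcome measures and describes its recording, and the same section has a five-point rating of overall pain intensity. This stands, and it limits the point: what is missing is a defined continuous VAS endpoint with a change score, time points and a comparison.

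Second, section 7.1 names tests of means, so some full-scale analysis may be intended, and an analysis plan that is not shown may spell it out. That plan may supply models and detail. But section 2.4.2 is itself the list of endpoints and it leaves VAS out, and section 7.1 does not say which variable its tests apply to. This part does not remove the point.

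Third, a reader might infer from step 4 that the cut costs the trial a fixed 14 to 17 points of power, or most of its information. The documents support neither. The protocol gives no SD, mean difference, VAS-ODI correlation or distribution. The loss arises only if the primary test compares proportions, and steps 5 and 6 show that it can be small or negative. Even in the favourable model most of the information is kept, and ODI and SF-36 remain continuous secondary endpoints.

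Fourth, a reader might infer that the responder primary should be replaced. A responder endpoint is a legitimate choice, and this protocol is built around it: the sample size (section 7), surgery for severe sciatica counted as failure (section 1.7) and the worst-case missing-data analysis (section 7.2). A score-based primary would need new rules for the last two and a sample size based on an SD that the documents do not contain. Statisticians would disagree on that trade-off, so it is not part of this point.

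**Conclusion.** The point holds as an omission in the endpoint list, joined to an unresolved conflict over the primary test. The omission can be read directly from sections 2.3.1, 2.4.2, 4.2 and 6.1 and rests on no assumption. So can the conflict: sections 2.4.1, 4.1 and 7 describe a responder comparison, while section 7.1 names only methods for means.

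The power figures are illustrative. The 80% against 94% (26 per arm) and 71% against 88% (21 per arm) depend on one normal score, equal SDs, a two-sided test and a shift of 0.99 SD. They show why a full-scale VAS analysis may be worth having beside the responder rate. They do not measure a loss that this trial will suffer. They also show that an unadjusted t test alone would be a fragile choice if the scores are heavy-tailed.

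The correction is worth making because it costs no data. It is not a reason to doubt the responder endpoint as primary.

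**What to change.** 1. In section 2.4.2, add change in VAS (mm) from baseline to 1, 3, 6, 12 and 24 months to the continuous measures, with month 24 as the leading secondary time point. Say which VAS reading is meant, since section 4.2 describes readings at rest and in motion and records them in centimetres.
2. In section 7.1, state that VAS, ODI and SF-36 are each analysed with a baseline-adjusted model (ANCOVA or repeated measures) that includes the rehabilitation stratum used in randomisation (section 2.2), with a rank-based analysis as a check. The regression in section 7.2 does not do this: it is a sensitivity analysis for covariates that turn out to differ at baseline and for rehabilitation during follow-up.
3. In section 7.1, state that the primary responder endpoint is tested by a comparison of proportions. Keep that endpoint as primary.

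The cost is an amendment to the wording, made before unblinding. VAS, ODI and SF-36 are already scheduled at every visit concerned, so no patients, visits or measurements are added.
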